### Instruments

#### Primary measures

The following instruments will be used:State-Trait Anxiety Inventory (STAI) [72, 86]. The STAI measures a person’s situational (or state) anxiety, as well as the amount of anxiety a person generally feels most of the time (trait). The two self-report scales contain 20 items each.Hamilton Anxiety Rating Scale (HAM-A) [33]. The HAM-A is an interviewer-administered and rated measure of the severity of anxiety symptoms. The scale consists of 14 items, each defined by a series of symptoms, and measures both psychic anxiety (mental agitation and psychological distress) and somatic anxiety (physical complaints related to anxiety).Clinical Global Impression - Severity scale (CGI-S) [32]. The CGI-S is a seven-point scale which requires that the clinician rate the severity of the patient’s illness at the time of assessment, relative to the clinician’s past experience with patients who have the same diagnosis.Clinical Global Impression - Improvement scale (CGI-I) [32]. The CGI-I is a seven-point scale which requires that the clinician assess how much the patient’s illness has improved or worsened, relative to a baseline state at the beginning of the intervention.Mini-International Neuropsychiatric Interview 5 (MINI) [51, 71]. The MINI is a short diagnostic interview based on the DSM-IV criteria, which focus on the existence of current psychiatric disorders. It consists of separate modules to diagnose specific disorders.

#### Secondary measures

The following instruments will be used:Structured Clinical Interview for DSM-IV Personality Disorders Questionnaire (SCID-II) [24, 25]. The SCID-II is an observer-based diagnostic interview used to determine DSM-IV Axis II disorders.Becks Depression Inventory II (BDI-II) [8]. The BDI-II is a 21-item self-report inventory used to assess DSM-IV depressive symptoms. Each item consists of four statements indicating increasing symptom severity.Outcome Questionnaire (OQ-45) [28, 45]. The OQ-45 consists of 45 items and is designed to evaluate a broad range of psychological problems and symptoms of psychopathology. It contains three subscales: 1) symptom distress, 2) interpersonal relations; and 3) social role.Self-Esteem Scale (SES) [22, 67]. The SES is a 10-item self-report scale that measures global self-worth by measuring both positive and negative feelings about the self.Defense Style Questionnaire (DSQ-40) [1, 13]. The DSQ-40 is a 40-item self-report questionnaire designed to measure an individual’s propensity towards three various defense styles (mature, neurotic, and immature), along with 20 individual defense mechanisms.Personality Beliefs Questionnaire (PBQ) [7]. The PBQ is a 126-item self-report measure of beliefs associated with 10 DSM-III-R and DSM-IV personality disorders (represented as subscales): 1) avoidant; 2) dependent; 3) obsessive-compulsive; 4) histrionic; 5) passive-aggressive; 6) narcissistic; 7) paranoid; 8) schizoid; 9) antisocial, and 10) borderline.Inventory of Interpersonal Problems (IIP) [37]. The IIP is a 64-item self-report questionnaire that inventories the interpersonal problems that people experience. It contains eight scales that assess different aspects of an individual’s interpersonal difficulties: 1) domineering/controlling; 2) vindictive/self-centered; 3) cold/distant; 4) socially inhibited; 5) non-assertive; 6) overly accommodating; 7) self-sacrificing; and 8) intrusive/needy.Dysfunctional Working Models Scale (DWM-S) [54, 62]. The DWM-S is a 35-item self-report measure of dysfunctional working models of the self and others.Experiences in Close Relationships (ECR) [14, 74]. The ECR is a 36-item self-report measure of adult attachment. It groups people into four different categories on the basis of scores along two scales: avoidance and anxiety.Bell Object Relations and Reality Testing Inventory (BORRTI) [10, 73]. The BORRTI is a 45-item self-report measure designed to evaluate the ability to sustain essential relationships and to accurately identify internal and external reality.Meta-Cognitions Questionnaire (MCQ) [17, 29]. The MCQ is a 65-item self-report scale developed to assess several dimensions of metacognition that is thought to be relevant to psychopathology. Its five subscales are: 1) positive beliefs about worry; 2) negative beliefs about thoughts concerning uncontrollability and danger; 3) cognitive confidence (assessing confidence in attention and memory); 4) negative beliefs concerning the consequences of not controlling thoughts, and 5) cognitive self-consciousness (the tendency to focus attention on thought processes).Satisfaction With Life Scale (SWLS) [20, 41]. The SWLS is a five-item self-report global measure of life satisfaction.Credibility/Expectancy Questionnaire (CEQ) [18]. The CEQ is used to measure expectancy for change and treatment credibility as potential confounds for outcome. It is comprised of six questions.

### Record retention and confidentiality

Epidemiological, clinical, and all outcome data from each patient will be recorded in an electronic database by a clinician responsible for the study. All records will be stored for 10 years from the date of the last study publication. All computer databases will include a unique participant identifier and not the participant’s name and address. Consent forms and other documents, including the participant’s name, will be stored separately from the questionnaires and other trial documents in locked cabinets.

### Withdrawal from the trial

Participants may voluntarily withdraw from the trial for any reason. A patient’s withdrawal from the trial will not affect that patient’s access to treatment.

### Sample size calculation

The sample size calculation was based on previous trials showing the effectiveness of group CBT or psychodynamic group therapy in anxiety and personality disorders; however, very few studies of this kind have been conducted. Additionally, we decided to base our study on trials showing the effectiveness of group psychotherapy in general, and on trials showing the effectiveness of group psychotherapy in day hospitals.

Burlingame *et al*. [15] estimated the effectiveness of group psychotherapy in a meta-analysis of 111 experimental and quasi-experimental studies that were published over the past 20 years. Based on 51 studies which compared active group treatment versus a wait-list control, the reported average effect size was 0.58. Effect sizes for comparisons with a wait-list control for different diagnoses and therapeutic orientations were not reported. Petrocelli [62] employed a meta-analysis to examine the effectiveness of GCBT based on 12 studies, in which GCBT was compared with no treatment. The average weighted mean effect size for GCBT versus no treatment was 0.59. Wersebe *et al*. [82] conducted a meta-analysis for the effectiveness of GCBT for social anxiety disorder. The inclusion of 11 RCTs comparing interventions with control conditions showed a pooled effect size of 0.53 in favour of the interventions. A review conducted by the Centre for Psychological Services Research at the University of Sheffield to assess evidence for the efficacy and effectiveness of psychodynamic group therapy (including group analysis) identified 37 studies [11, 12]. Only one study included the wait-list control [78], but was limited to binge-eating disorder patients. Knijnik *et al*. [44] conducted an RCT which showed that patients with generalized social phobia treated with psychodynamic group therapy improved significantly on their social anxiety symptoms as compared to the placebo group, showing an effect size of 0.83. The most similar trials to ours are two RCTs reported in a Cochrane review which deal with group psychotherapy as a component of day treatment [2, 50, 63]. The first study found that day care patients suffering from affective disorders and personality disorders experienced a significant improvement as compared to patients in the wait-list control group [63]. The mean effect size for 17 outcome variables was 0.71. In the second study, day care treatment (18-week group psychodynamic and cognitive-behavioral psychotherapy) was compared to individual psychotherapy in patients with personality disorders [2]. No significant differences in improvement were observed between the two groups.

The effects of the intervention on symptoms of anxiety are the primary outcome measures in our study. Although the study’s general aim is to compare both treatments with the wait list, an additional comparison has been planned of both treatments on the outcomes. Comparison between all three groups is possible for two subsequent measurements. Due to ethical reasons, subjects from the wait list will start therapy soon after the second measurements and will not be available to participate in the study during the third measurement. As a result, that data will be analyzed in a 3 × 2 experimental plan (three groups available for two repeated measures) and in a 2 × 3 experimental plan (two groups available for three repeated measures). Based on the trials mentioned above, we assumed that we would be able to show the differences between the interventions and the control conditions with a standardized effect size of 0.58 (the lowest value effect size presented in the literature) for continuous outcomes. As this effect size was Cohen’s d suited for t-test comparisons, we conducted a conversion into f suited for analysis of variance (f = 0.29). The sample size was calculated using the G*power software program [23]. Assuming an alpha of 0.05, with a power (1-β) of 0.80, a minimum number of 96 patients is required for a 2 × 3 experimental plan, and a minimum number of 120 patients is required for a 3 × 2 experimental plan. Furthermore, for the purpose of being able to identify the difference between the two treatments, we followed the design of the most similar study [2] and assumed effect sizes of 0.24 for continuous outcomes, which leads to a total sample size of 171 participants for a 3 × 2 experimental plan and a total sample size of 140 participants for a 2 × 3 experimental plan. We will also test possible within-between group interaction, however its effect size is not available in literature. We assumed a medium effect size for the interaction (f = 0.25), which needs 156 participants in a 2 × 3 plan and 159 participants in a 3 × 2 plan. Assuming that there is a dropout rate of 25 %, this means that 199 participants will need to be recruited.

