### Objectives

The main objective of the planned research is to evaluate the clinical effectiveness of short-term, intensive, psychodynamic, and cognitive-behavioral group psychotherapy for anxiety disorders and comorbid depressive or personality disorders in day care conditions.

The more specific objectives are to: 1) show the effectiveness of each treatment in a day care setting relative to the wait-list control group; 2) demonstrate the relative short- and long-term effectiveness of the two active treatments; 3) carry out a preliminary examination of the predictors and moderators of treatment response; 4) carry out a preliminary examination of the mediators of therapeutic change; and 5) compare the impact of both methods of treatment on the outcome of the measures used in this study.

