## Discussion

This study examines whether day treatment based on short-term intensive group therapy is effective. A further objective is to examine which of the two therapy modalities, psychodynamic or cognitive-behavioral, is more effective. We also plan to examine the predictors, moderators, and mediators of therapeutic change. The current study has several strengths.

Despite a large number of RCT studies showing the advantages of using psychodynamic therapy and CBT for anxiety disorders and personality disorders [35, 70], there is still insufficient evidence for the efficacy of the group forms of these approaches, especially the psychodynamic orientation. Most studies show that the efficacy of treating anxiety disorders with cognitive-behavioral group therapy is comparable to its individual form [31, 53, 66, 69, 84]. There is still a lack of similar group versus individual comparisons for the psychodynamic approach [15].

A meta-analysis conducted by Tolin [79] that examined the effectiveness of CBT and other therapies showed the superiority of CBT over alternative therapies among patients with anxiety or depressive disorders. A recent meta-analysis by Baardseth *et al*. [3] showed no differences between CBT and non-CBT treatments for anxiety disorders. In those analyses, however, almost none of the trials were completed in community settings.

Group psychotherapy as day treatment differs from outpatient therapy in intensity (usually five sessions per week versus one session per week). To date, there have been only two RCTs [2, 63] comparing psychodynamic group psychotherapy and cognitive-behavioral group psychotherapy as components of day treatment with outpatient therapy. However, neither of the studies addressed anxiety disorders.

There have been several studies about the efficacy of day treatment of anxiety disorders in Poland [13, 49, 75, 83, 85]. These studies show promising results, however, none of them were RCTs. This will be the first RCT to evaluate manualized psychodynamic group therapy and cognitive behavioral group therapy in a day treatment setting for people with anxiety disorders. The design of the study overcomes the disadvantages of previous studies in that it provides a randomized controlled design, consists of a large sample size, adequate inclusion criteria, an adequate treatment protocol, and a clear separation of intervention conditions.

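### The effect size of 0.24 assumed for psychodynamic versus cognitive-behavioral therapy is not supported by the study cited for it, and 199 recruits do not give that comparison the 80% power implied

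*Protocol article*

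**What the plan says.** Objective 2 of the protocol article is to "demonstrate the relative short- and long-term effectiveness of the two active treatments". The section Sample size calculation sizes this comparison separately, with the stated aim of detecting a difference between the therapies: "we followed the design of the most similar study [2] and assumed effect sizes of 0.24 for continuous outcomes". The error rates are given just before: "Assuming an alpha of 0.05, with a power (1-β) of 0.80". The results are 171 for the 3 × 2 plan (three groups, two measurements) and 140 for the 2 × 3 plan (two therapy groups, three measurements).

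The same section describes study [2] as follows: "day care treatment (18-week group psychodynamic and cognitive-behavioral psychotherapy) was compared to individual psychotherapy in patients with personality disorders [2". Of its result the section says only this: "No significant differences in improvement were observed between the two groups". The Background describes the study in the same way. Of the two day-treatment trials it cites, one of which is study [2], the Discussion adds: "However, neither of the studies addressed anxiety disorders".

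For therapy against the wait list, the section takes d = 0.58 and converts it to f = 0.29. No metric or conversion is given for 0.24. The section ends with a 25% dropout allowance and 199 patients to be recruited.

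**The concern.** Study [2], as described, holds both modalities in one arm and varies format and setting: day group treatment against individual therapy. This trial does the reverse. Both arms share the day unit, the group format and the session frequency, and only the modality differs. A trial that pools the two modalities cannot inform the difference between them, yet it is the only support offered for 0.24.

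The article's other evidence on the question is in the Discussion and is split. One meta-analysis favoured CBT in anxiety or depressive disorders; a more recent one "showed no differences between CBT and non-CBT treatments for anxiety disorders". Neither is used for sizing.

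The second issue is whether the number recruited reaches the number required. If it does not, the reader is left with an impression of 80% power for objective 2 that the trial will not have, and with no statement of how large a difference it could detect.

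**Working it through.** **Inputs.** From Sample size calculation: alpha 0.05, power 0.80, effect sizes 0.58 and 0.24, totals 96, 120, 140 and 171, dropout 25%, 199 recruited. The allocation ratio is not stated; 1:1:1 is assumed here.

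**Method.** One-way F test with k equal groups and total N: noncentrality λ = N × f², degrees of freedom (k − 1, N − k). For two equal groups, f = d/2.

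**Step 1: reproduce the protocol's figures.**

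| f | k | N stated | λ = N × f² | Power |
|---|---|---|---|---|
| 0.29 (= 0.58/2) | 2 | 96 | 8.07 | 0.803 |
| 0.29 | 3 | 120 | 10.09 | 0.809 |
| 0.24 | 2 | 140 | 8.06 | 0.805 |
| 0.24 | 3 | 171 | 9.85 | 0.802 |

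All four are the smallest equal-group totals reaching 0.80, so 0.24 was entered as Cohen's f. Repeated-measures formulas with correlations from 0 to 0.9 do not give 140 and 171. If 0.24 were a Cohen's d, then f = 0.12, power at 140 would be 0.29, and 548 patients would be needed.

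**Step 2: what f = 0.24 means for two arms.** d = 2 × 0.24 = 0.48, and 0.48/0.58 = 0.83. The two therapies are assumed to differ from each other by 83% of what therapy is assumed to gain over waiting.

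**Step 3: what the planned size delivers.** The 199 equals 159 × 1.25 = 198.75, rounded up. The 159 comes from the interaction calculation (f = 0.25), not from the 0.24 calculation. Then:

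- in the two therapy arms at randomization: 199 × 2/3 ≈ 133; λ = 133 × 0.0576 = 7.66; power 0.785;
- after 25% dropout: 133 × 0.75 ≈ 100; λ = 5.76; power 0.66;
- to retain 140 in those two arms: 140/0.75 = 187 would have to be randomized to them alone.

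**Step 4: detectable difference.** With two groups and 80% power, the smallest detectable d is about 0.48 at N = 140 and about 0.57 at N = 100.

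**Step 5: sensitivity to the true difference.** No document gives a modality-versus-modality estimate, so only a range can be shown.

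| True d | Power at N = 140 | Power at N = 100 |
|---|---|---|
| 0.20 | 0.22 | 0.17 |
| 0.30 | 0.42 | 0.32 |
| 0.40 | 0.65 | 0.51 |
| 0.48 | 0.805 | 0.66 |
| 0.60 | 0.94 | 0.84 |

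**The case against.** - **Power is conditional on the assumed effect.** At f = 0.24, 140 patients in two groups give 80.5% power wherever the value came from. This stands. A reader might infer that the mismatch with study [2] makes the power calculation inapplicable; it does not. It removes the justification, not the arithmetic.
- **The text says that 0.24 was assumed.** It reports no effect size for study [2], so one cannot say that 0.24 is the effect observed there. This also stands. But 0.24 is not presented as a minimum relevant difference either, and study [2] is its only stated basis.
- **The populations overlap.** A comorbid personality or depressive disorder is required for entry (Table 1), and the Background reports a personality disorder in 82.3% of one of the team's own samples. That softens the population mismatch but leaves the mismatch of contrast untouched.
- **The comparison is described as additional.** The primary planned comparisons are each therapy against the wait list, and 199 does not depend on 0.24. True, and it limits the weight of the point; but this is still objective 2, with its own stated sample size.
- **Wait-list patients are re-randomized to the therapies after waiting.** If all were added, about 199 × 0.75 ≈ 149 would remain and power would be 0.83. However, the sample-size section says that wait-list patients will not be available at the third measurement, so the 2 × 3 plan does not count them.
- **The analysis uses repeated measures, which could be more efficient.** For instance, a between-group test averaged over three measurements needs 94 patients at f = 0.24 if the correlation is 0.5, and 112 if it is 0.7. The protocol gives no correlation, and its own totals are not based on such a model.

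Two other inferences lack support. No passage plans to read a non-significant result as equal effectiveness. Nor does anything justify shrinking the effect in proportion to the shared sessions in Table 2, which belong to both manuals and are meant to intensify the therapeutic processes.

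**Conclusion.** The point holds in two limited parts. First, study [2], as the protocol describes it, does not support 0.24 as a difference between psychodynamic and cognitive-behavioral group therapy; the value is an assumption without a source for this contrast. Second, the calculation is correct for that assumption, but the planned size falls short of it: power is about 0.785 with about 133 patients in the two therapy arms and about 0.66 with about 100 after dropout, against the 0.80 implied. The detectable difference is then about d = 0.57, not 0.48.

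These figures rest on 1:1:1 allocation, on the one-way F model that reproduces the protocol's totals, on the protocol's own 25% dropout, and on not counting wait-list patients re-randomized after waiting. The primary comparisons with the wait list are not affected by this point.

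**What to change.** In Sample size calculation:

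- State that 0.24 is Cohen's f (d = 0.48 for two groups), that it is an assumption, and that it is not derived from a comparison of modalities. Remove study [2] as its support.
- Replace the implied 80% power for the two-therapy comparison with the smallest difference detectable with 80% power at the number expected to be retained in the two therapy arms: about d = 0.57 at 100, against 0.48 at 140. State the allocation ratio and whether re-randomized wait-list patients count towards that number.

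In Statistical analysis, say that objective 2 will be reported as the estimated difference between the two therapies with its 95% CI.

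The cost is wording only, with no added patients or visits. The downside is that the stated power for this additional comparison becomes less favourable.

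### The 171 patients given for detecting a difference between the two therapies is the size of a three-group test that includes the wait list; the matching two-therapy figure is the protocol's own 140, counted in the two therapy arms alone

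*Protocol article*

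**What the plan says.** All the figures are in the protocol article, Sample size calculation. Two analysis layouts are defined. The 3 × 2 plan has "three groups available for two repeated measures"; the 2 × 3 plan has "two groups available for three repeated measures", because wait-list patients have started therapy by the third measurement. The general setting is "Assuming an alpha of 0.05, with a power (1-β) of 0.80".

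For interventions against control, the standardized effect of 0.58 is converted to f = 0.29, and "a minimum number of 96 patients is required for a 2 × 3 experimental plan"; the 3 × 2 plan is given 120.

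Then, "for the purpose of being able to identify the difference between the two treatments", the authors "assumed effect sizes of 0.24 for continuous outcomes". They report that this "leads to a total sample size of 171 participants for a 3 × 2 experimental plan". For the layout without the wait list, the same sentence gives a smaller number: "a total sample size of 140 participants for a 2 × 3 experimental plan".

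The section calls the therapy comparison additional to the main aim of comparing each therapy with the wait list. Even so, relative short- and long-term effectiveness of the two therapies is the second specific objective under Objectives. Under Statistical analysis, the primary planned contrasts are each therapy against the wait list.

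**The concern.** Two sample sizes are attached to questions that their tests do not ask.

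- A test across three groups has the null hypothesis that both therapies and the wait list are all equal. It can reject solely because the wait list does worse. A sample size for that test says nothing definite about power to separate the two therapies.
- The 2 × 3 plan holds only the two therapies. A sample size from it cannot be the number needed to show that a therapy beats the wait list.

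At stake is what the trial can claim about a declared objective. A reader would take 171 patients in total as giving 80% power for the head-to-head comparison, and might take a significant three-group result as evidence on it.

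**Working it through.** **Inputs from the document:** alpha 0.05; power 0.80; f = 0.29 (from d = 0.58); effect size 0.24, metric not named; three groups in the 3 × 2 plan and two in the 2 × 3 plan; 25% dropout; 199 recruited. **Assumptions:** 1:1:1 allocation (the ratio is not stated) and no re-randomised wait-list patients in the therapy comparison.

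**Step 1. Reproduce the stated figures.** Power = P(F′ > F_crit), where F′ is noncentral F with λ = f²·N, numerator df = groups − 1 and denominator df = N − groups. N is rounded up to equal groups.

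| f | Groups (numerator df) | N | λ | Power | Protocol |
|---|---|---|---|---|---|
| 0.24 | 3 (2) | 171 | 9.85 | 0.802 | 171 |
| 0.24 | 2 (1) | 140 | 8.06 | 0.805 | 140 |
| 0.29 | 3 (2) | 120 | 10.09 | 0.809 | 120 |
| 0.29 | 2 (1) | 96 | 8.07 | 0.803 | 96 |

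All four match. So 0.24 acts as f, which for two equal groups means d = 2 × 0.24 = 0.48. The 171 is a three-group omnibus size; 140 and 96 are two-group sizes. The usual repeated-measures formula for the between-group factor at correlation 0.5 gives 129 and 94 in place of 171 and 140, so it is not what was used.

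**Step 2. What the three-group test responds to.** Let the therapies be identical and both 0.58 SD better than the wait list. Then f² = 0.58² × 2/9 = 0.0748, so f = 0.273 and λ = 0.0748 × 171 = 12.8. The test rejects with probability 0.90. The stated 80% is reached with equal therapies that are 0.24 × 3/√2 = 0.51 SD better than the wait list, with no therapy difference at all.

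**Step 3. Power of the direct contrast, same formula, f = 0.24, 1 df.**

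- 171 in total: 171 × 2/3 = 114 in the two therapies (57 per arm). λ = 0.0576 × 114 = 6.57; power 0.72.
- 199 recruited: 199 × 0.75 = 149.25 remain, of whom two thirds, about 100, are in the therapies (50 per arm). λ = 5.76; power 0.66.
- 80% requires 140 in the two therapies, or 140 × 3/2 = 210 across three equal arms before dropout.

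**Step 4. Dependence on the pre-post correlation ρ.** For change scores the standardized difference is 0.48/√(2(1 − ρ)).

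| ρ | Difference in change-score SDs | Power, 57 per arm |
|---|---|---|
| 0.3 | 0.406 | 57% |
| 0.5 | 0.480 | 72% |
| 0.6 | 0.537 | 81% |
| 0.7 | 0.620 | 91% |

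The ρ = 0.5 row equals the Step 3 result because √(2 × 0.5) = 1.

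**Step 5. The 96.** It is a 1-df size at f = 0.29 for the two groups in the 2 × 3 plan, both of which are therapies. Read literally, it is the size for a 0.58 SD difference between the therapies, whereas the effect sizes near 0.58 that the section cites are against control or no treatment.

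**The case against.** The strongest reply is that the sentence giving 171 also gives 140 for the two-group plan, and 140 is a correctly matched size for the therapy comparison at f = 0.24. That stands. A reader might infer that the protocol has no valid size, or no planned analysis, for the head-to-head question; the document does not support this. With two groups, the group and group-by-time effects of the 2 × 3 plan are the CBT-versus-PDT comparison. But 140 does not rescue 171, which puts only 114 patients in those two arms.

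A reader might also take the 90% in Step 2 as a false-positive rate. It is not. The three-group null is false in that scenario, so the rejections are correct. They would mislead only if read as a therapy difference, and the document nowhere says that they will be.

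Nor can it be said that 80% power is out of reach. With 57 per arm, change-score power passes 80% at a correlation of about 0.6. Much lower power (about 25% with 57 per arm) would follow if 0.24 were Cohen's d, but the protocol's own 171 and 140 show it working as f.

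The Participant recruitment section has wait-list patients randomised to the two therapies after waiting. If they counted, about 149 would be in the comparison, with power about 0.83. Against this, the sample size section says they are not available at the third measurement, and the 3 × 2 plan counts them as wait list.

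Finally, 199 follows from the interaction figure (159 × 1.25 = 198.75), so neither 171 nor 96 sets the recruitment target. That stands, and it limits the point to what the figures are said to deliver.

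**Conclusion.** The point holds in a limited form. The 171 is an omnibus size that includes the wait list and does not give 80% power for CBT versus PDT. On the formula behind the protocol's own figures, the direct contrast has power of about 0.72 at 171 in total and about 0.66 at 199 less 25% dropout. The 96 cannot be a size for intervention versus control. The 140 is sound, provided it is read as patients in the two therapy arms together.

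The power values rest on 1:1:1 allocation, on 0.24 being f, and on leaving re-randomised wait-list patients out; they also move with the pre-post correlation. The mismatch between test and question depends on none of these.

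**What to change.** In Sample size calculation:

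- Remove 171 as the size for the therapy difference and 96 as a size for intervention versus control.
- Keep 140 and state that it counts the two therapy arms only.
- State that the therapy comparison rests on the direct 1-df CBT-versus-PDT contrast, and that a significant three-group test supports no statement about it.
- Report the power of that contrast at the planned number per arm, naming the metric of the assumed effect size and the assumed correlation.

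The cost is a reworded paragraph and one named contrast, with no extra patients. The downside is that the stated power for the therapy comparison becomes less favourable unless the correlation is about 0.6 or higher (at 57 per arm).

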**Methods/Design:**

In this randomized controlled trial, a total of 199 patients with anxiety disorders and comorbid depressive and/or personality disorders will be assigned to one of three conditions: 1) psychodynamic group therapy; 2) cognitive-behavioral group therapy; or 3) wait-list control group. The therapy will last 12 weeks. Both treatments will be manualized (the manuals will address comorbidity). Primary outcome measures will include self-reported symptoms of anxiety, observer-rated symptoms of anxiety, global improvement, and recovery rate. Secondary outcome measures will include the number of pathological personality traits, depression, self-esteem, defense mechanisms, beliefs about self and others, interpersonal problems, object relations, parental bonding, meta-cognition, and quality of life. Measures will be taken at baseline, post-treatment, and at six months following the end of therapy.

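### The target of 199 multiplies by the dropout rate instead of dividing, passes over the larger 171, and sets two-arm sizes against a three-arm total

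*Protocol article*

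**What the plan says.** The protocol article, under Sample size calculation, sets the operating characteristics as follows: "Assuming an alpha of 0.05, with a power (1-β) of 0.80". It then gives six minimum sizes.

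- At f = 0.29, converted from d = 0.58 for therapy against control: "a minimum number of 96 patients is required for a 2 × 3 experimental plan"; the 3 × 2 plan needs 120.
- At 0.24, for the difference between the two therapies: "which leads to a total sample size of 171 participants" in the 3 × 2 plan, and 140 in the 2 × 3 plan.
- At f = 0.25, for the within-between interaction: "which needs 156 participants" in the 2 × 3 plan, and 159 in the 3 × 2 plan.

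The 3 × 2 plan has three groups and two measurements. The 2 × 3 plan has two groups and three measurements, because wait-list patients have started therapy by then and are not available at the third measurement. The section ends with a 25% dropout assumption and the statement that "this means that 199 participants will need to be recruited". The Abstract (Methods/Design) confirms that this is the total across all three conditions: "a total of 199 patients with anxiety disorders".

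**The concern.** A recruitment target should leave the required number of patients after the expected losses, and it should be built on the largest size the plan intends to meet. The figure of 199 does neither for four of the six sizes. It also does not allow for the fact that two of those four concern only two of the three arms.

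The comparison most exposed is therapy against therapy. The relative short- and long-term effectiveness of the two treatments is the second objective, and its long-term part rests wholly on the 2 × 3 plan. A reader who takes the stated 80% power at face value could read a null result there as evidence that the therapies are alike, when the plan's own assumptions do not give that power. The three-arm interaction matters too, because the Statistical analysis section makes time by group the primary planned comparison.

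**Working it through.** **Inputs.** Alpha 0.05, power 0.80, the effect sizes f = 0.29, 0.24 and 0.25, the six minima, 25% dropout and the target of 199 all come from Sample size calculation. The spread over three conditions comes from the Abstract. The allocation ratio is not stated; 1:1:1 is assumed.

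**Step 1: reproduce the plan's minima.** Use a noncentral F test with noncentrality λ = f² × N, and round N up to equal groups.

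- Between groups, df = k − 1 and N − k. f = 0.29 gives 96 (k = 2) and 120 (k = 3). f = 0.24 gives 140 (k = 2) and 171 (k = 3).
- Interaction with m measurements, df = (k − 1)(m − 1) and (N − k)(m − 1). f = 0.25 gives 156 (2 × 3) and 159 (3 × 2).

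All six match exactly, so the sponsor's method is identified.

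**Step 2: reproduce 199.** 159 × 1.25 = 198.75, rounded up to 199. The other routes give different numbers: 159/0.75 = 212; 171 × 1.25 = 213.75, or 214; 171/0.75 = 228; 156 × 1.25 = 195; 156/0.75 = 208. So the base was 159 and the dropout was multiplied.

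**Step 3: what 199 leaves.**

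- Three arms: 199 × 0.75 = 149.25, about 149. This is below 159 and 171 and above 120.
- Two therapy arms at 1:1:1: 199 × 2/3 = 132.7, about 133 randomized. Then 199 × 2/3 × 0.75 = 99.5, about 100 completers. The 133 is already below 140 and 156; the 100 is above 96.

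**Step 4: power at those sizes, same formula.**

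| Test | Stated minimum | Completers: N, power | All randomized: N, power |
|---|---|---|---|
| 3 × 2, f = 0.29 | 120 | 149, 0.89 | 199, above 0.89 |
| 2 × 3, f = 0.29 | 96 | 100, 0.82 | 133, above 0.82 |
| 3 × 2 interaction, f = 0.25 | 159 | 149, 0.78 | 199, 0.89 |
| 3 × 2, f = 0.24 | 171 | 149, 0.74 | 199, 0.86 |
| 2 × 3, f = 0.24 | 140 | 100, 0.66 | 133, 0.78 |
| 2 × 3 interaction, f = 0.25 | 156 | 100, 0.60 | 133, 0.73 |

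**Step 5: totals that would meet each missed minimum after 25% dropout.** Three-arm sizes: 159/0.75 = 212 and 171/0.75 = 228. Two-arm sizes scaled to three equal arms: 140 × 1.5/0.75 = 280 and 156 × 1.5/0.75 = 312.

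**The case against.** Several points can fairly be made for the plan.

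- **The main aim is covered.** The section calls comparison with the wait list its general aim and therapy against therapy an additional comparison. Both f = 0.29 sizes survive dropout, and the 3 × 2 interaction falls only from 0.80 to 0.78. This stands. A reader might infer that 199 misses every minimum, or that the trial is underpowered for its main question; the figures do not support that.
- **Intention to treat.** The Statistical analysis section analyzes all randomized patients, with multiple imputation when appropriate, alongside completers. If all 199 counted fully, 159 and 171 would be exceeded. That is an upper bound, because imputation does not restore all lost information and the plan itself inflates for dropout. Even then, at 1:1:1 the therapy arms miss 140 and 156.
- **The method is conservative.** λ = f² × N takes no credit for repeated measures. For the between-group test, the usual factor m/(1 + (m − 1)ρ) exceeds 1 for any correlation ρ below 1. At an assumed ρ of 0.5, f = 0.24 gives 0.83 with 100 patients (2 × 3) and 0.86 with 149 (3 × 2). The protocol states no correlation. It would therefore be wrong to read 0.60 to 0.66 as the trial's actual power; these values are what the plan's own method yields.
- **Other allocation.** At 2:2:1 the therapy arms would hold 199 × 0.8 = 159 randomized, enough for 140 and 156 before dropout, but 159.2 × 0.75 = 119 after it, below both.
- **Re-randomized wait-list patients.** The recruitment section says they are later randomized to the two therapies. Pooling them would give about 149 completers, which meets 140 but not 156. The sample size section says they are unavailable at the third measurement, so pooling is not the evident intention.

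None of this explains the multiplication by 1.25 or the silence about 171.

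**Conclusion.** The paragraph is wrong as written, in three ways: dropout is multiplied (199 where 159 requires 212), the larger 171 is not carried forward and no reason is given, and two-arm sizes are covered by a three-arm total. The first two follow from the section's own figures without any assumption. The third rests on 1:1:1 allocation for its exact size.

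The consequence is uneven. It is nil for the f = 0.29 sizes, small to moderate for the other three-arm tests, and substantial for therapy against therapy. The completer powers are conditional on 25% dropout, equal allocation and the sponsor's formula.

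A reader might also infer that 312 patients must be recruited. That total would meet all six stated sizes under equal allocation, but the documents do not say that every one of them was meant to bind, so it is not a requirement the plan has set itself.

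**What to change.** Correct the sample size paragraph, and the total in the Abstract if it changes:

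1. Divide by 0.75 rather than multiply by 1.25.
2. State which minimum sets the target, and why 171 is or is not it.
3. Label 96, 140 and 156 as patients in the two therapy arms, and give the allocation ratio.
4. If 199 stays, restate the power it gives for each test, naming the method, allocation and analysis set, and say that therapy against therapy does not reach the stated 80% under the plan's own assumptions.
5. Reconcile the re-randomization of wait-list patients (recruitment section) with their unavailability at the third measurement (sample size section), and say whether their later data enter the therapy comparison.

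If the figures are restated and the target is kept, the cost is one reworded paragraph, a less favourable stated power and no extra patients.
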